#### Aim 3: Pilot Trial of the Intervention Packages

##### Overview

The aim of this phase of the project is to pilot the coproduced intervention packages developed in phase 2 of the project to assess their feasibility, acceptability, cost, and potential effectiveness. This phase will also assess the factors that facilitated and hindered the implementation of the piloted intervention packages and what needs to be learned before scaling up.

The pilot of the ARISE&WIN interventions has been planned as a quasi-experimental study with a prepost design. The design was chosen because there was unanimity around it being feasible while allowing us to draw conclusions about the potential effectiveness of various interventions. The study will consist of 3 arms. One of the intervention groups will receive the capacity building intervention package. The second intervention group will receive the social protection intervention package in addition to the capacity building intervention package. The capacity building and the social protection interventions will be finalized during the coproduction process. The third group will be a control group serving as a comparison group, and participants will not receive any intervention. The pilot will be conducted in the LGAs of Greater Ibadan, where situational analysis has been conducted. The LGAs will be stratified into urban, periurban, and rural LGAs and randomly assigned to 1 of the 2 intervention groups or the control group. On the basis of recommendations from literature [43,44] on pilot trials, a sample size of 120 participants would be large enough to assess feasibility and other outcomes of interest in the pilot study. To account for possible attrition, the sample size would be rounded up to 150 in total, with 50 participants per arm of the trial. Frequency matching will be conducted to ensure that across the intervention and control LGAs, the participants will have similar characteristics based on age and their sector of occupation. Participants will be recruited through advertisements on social media platforms where self-employed young women are active. Announcements will also be made at business association meetings to identify eligible participants. Participants will also be recruited through partner organizations (SMEDAN and the Centre for Support of Women in Unpaid and Informal Employment in Nigeria) that work with self-employed young women.

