All groups will participate in a preintervention survey. Then, the interventions will be delivered over a period of 4 months. Follow-up surveys will be conducted at 6 weeks at the end of the capacity building intervention and months 4, 6, and 12. As part of a process evaluation, in-depth exit interviews will be conducted with approximately 20 participants to gain deeper insights into their perceptions about the interventions they receive. In addition, a survey will be administered to intervention facilitators while a subset of them will participate in in-depth interviews.

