##### Analysis

Participants’ background characteristics will be summarized using frequencies and percentages for categorical variables, such as education, religion, marital status, etc. Means and SDs will be computed for numerical variables, such as age and income. The comparison of study outcomes across the 3 groups will be done using chi-square tests and 1-way ANOVA, as appropriate, at *P*<.05. Pairwise comparisons will also be done to compare the 2 intervention groups with the control group. Bonferroni adjustment will be made to correct for error rates that may be introduced by multiple comparisons. If necessary, generalized linear models will be fitted to adjust for confounders and pertinent variables that exhibit baseline differences between the study groups (eg, education status). Descriptive statistics and multivariate regressions will be adopted to analyze the Likert-scale questions in the survey on the feasibility and acceptability of the interventions to the participants and facilitators. All qualitative data in the study will be analyzed using the reflexive thematic analysis method.

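### The rule for covariate adjustment leaves the final model to be chosen after the baseline data are seen, by observed imbalance rather than expected relation to the outcome

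*Protocol article*

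**What the plan says.** In the Analysis section under Aim 3, the outcome comparison is unadjusted: "The comparison of study outcomes across the 3 groups will be done using chi-square tests and 1-way ANOVA, as appropriate, at *P*<.05". Pairwise comparisons with control follow, with a Bonferroni correction. Adjustment is conditional: "If necessary, generalized linear models will be fitted to adjust for confounders and pertinent variables that exhibit baseline differences between the study groups". One example is given in parentheses, "eg, education status". The section does not say what makes adjustment necessary or what counts as a difference, and it fixes no covariate.

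The Aim 3 Overview gives the design facts that bear on this:
- The pilot is "planned as a quasi-experimental study with a prepost design".
- Allocation is by area: "The LGAs will be stratified into urban, periurban, and rural LGAs and randomly assigned to 1 of the 2 intervention groups or the control group".
- Frequency matching is meant to ensure that "the participants will have similar characteristics based on age and their sector of occupation".
- Baseline measurements will exist for every arm: "All groups will participate in a preintervention survey".

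The Analysis section does not place age, sector, area stratum or the baseline value of an outcome in any model.

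**The concern.** Three things go wrong when observed imbalance decides adjustment.

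1. **Wrong criterion.** A covariate biases the comparison, or costs precision, in proportion to its relation with the outcome. A visible imbalance in a variable unrelated to the outcome does no harm. A modest imbalance in a strong predictor does harm and is easily overlooked at this sample size.
2. **Conflict with the design.** Age and sector were important enough to match on. If the matching succeeds they will show little difference between arms, so the rule passes them over.
3. **Open choice of model.** With both the need and the difference undefined, whether to adjust and for what are settled after the data are seen. A reader cannot tell which result was planned.

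Real baseline differences are plausible here. Whole LGAs are allocated, and women are recruited through advertisements, associations and partner organisations. Potential effectiveness is a stated aim, and the Discussion says the results will be used to refine the packages before a large efficacy trial.

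**Working it through.** The protocol gives no figure for this rule, so there is none to reproduce. The steps below illustrate how it behaves.

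**Inputs from the document.** Three arms; 50 per arm (150 in total, Aim 3 Overview); 120 before allowance for attrition, so 40 per arm; 300 in the Abstract, so 100 per arm if equal. The 150 and the 300 conflict, so each is shown.

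**Assumptions not in the document.** A difference counts as exhibited when a baseline 1-way ANOVA gives P<.05; one arm is truly shifted by 0.3 SD; covariate-outcome correlation is 0.3 or 0.5; clustering by LGA is ignored.

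**Step 1: chance of noticing the shift.** With one of three arms shifted by d, the F test has noncentrality λ = n·d²·(2/3) on 2 and 3n−3 degrees of freedom. At n = 50 and d = 0.3, λ = 50 × 0.09 × 2/3 = 3.0.

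| Per arm | λ | 5% critical F | Detected | Missed |
|---|---|---|---|---|
| 40 | 2.4 | 3.07 | 26% | 74% |
| 50 | 3.0 | 3.06 | 32% | 68% |
| 100 | 6.0 | 3.03 | 58% | 42% |

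At 50 per arm, shifts of 0.2, 0.4 and 0.5 SD are missed 84%, 48% and 27% of the time.

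**Step 2: what the missed shifts leave behind.** Simulation, 6,000 runs per row, no true effect, 0.3 SD shift. Bias is for the shifted arm against another arm, in outcome SDs. Type I error is for that single comparison at two-sided 5%, before Bonferroni.

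| Per arm | Correlation | Bias: never / if flagged / always adjusted | Type I error: never / if flagged / always adjusted |
|---|---|---|---|
| 50 | 0.3 | 0.095 / 0.050 / 0.005 | 7.4% / 5.6% / 4.8% |
| 50 | 0.5 | 0.152 / 0.077 / 0.001 | 11.7% / 6.6% / 5.4% |
| 100 | 0.3 | 0.090 / 0.023 / −0.001 | 9.6% / 5.6% / 4.9% |
| 100 | 0.5 | 0.153 / 0.041 / 0.002 | 19.2% / 6.5% / 5.1% |

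Checks: unadjusted bias should equal correlation × shift, which is 0.3 × 0.3 = 0.09 and 0.5 × 0.3 = 0.15, as found. Direct calculation of the unadjusted type I error at 50 per arm gives 7.3% and 11.6%, in line with the simulation. Simulation error is about √(0.05 × 0.95/6000) = 0.3 percentage points on the error rates and 0.003 SD on the bias, so 5.6% is only just distinguishable from 5%.

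**Step 3: matched factors.** If sector counts are identical in each arm, the chi-square statistic is 0 and P = 1.00. In one example with 8 to 12 women per cell, P = 0.99. For age, with equal counts per age band in each arm at 50 per arm (5,000 runs; the bands are assumed), ANOVA flagged a difference in 0.0% of runs with four bands and 0.02% with two. With two wide bands and one arm skewed within them, it flagged 5.5%.

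**The case against.** **The plan contains no baseline significance test.** Correct. It describes background characteristics with frequencies, percentages, means and SDs. A reader might infer that variables will be screened at 5%, but the document does not say so. The miss rates therefore illustrate one reading of the rule. An undefined judgement is no less dependent on the data, so the main point stands.

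**The sentence may cover two classes of variable.** Confounders may be one class and imbalanced variables another. That reading is grammatically open, so it goes too far to say that covariates enter only when they differ at baseline. It does not rescue the rule: the opening conditional governs both classes, no confounder is named in advance, and a factor balanced by matching would hardly be treated as confounding the group comparison.

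**Education is not called prognostic.** Correct. It appears as an example of a variable that might differ.

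**Leaving out matched factors need not make the standard error too large.** This objection stands. If age and sector explained 5% to 15% of an outcome, omitting them would widen the standard error by 1/√(1−R²), or 3% to 8%. But allocation is by LGA. Assuming 10 women per LGA and an intracluster correlation of 0.02 to 0.05, the true standard error exceeds the ANOVA value by √(1 + 9 × 0.02) to √(1 + 9 × 0.05), or 9% to 20%. The document gives neither figure. The net direction may be the reverse, so none is claimed.

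**It is a pilot, and covariate lists usually belong in the analysis plan.** The stakes are indeed lower, and a missing list alone would be no finding. Here, though, the article states a selection criterion, and it is the criterion that is faulty.

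**Conclusion.** The point holds in a limited form. The adjustment rule is open to choice after baseline data are seen, uses imbalance as its guide, and is likely to pass over the two matching factors if matching succeeds. Coarse age bands or failed matching would weaken that last part.

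Under the assumptions above, the size is modest. At 50 per arm, bias is about 0.05 to 0.08 SD and type I error about 5.6% to 6.6%, for a 0.3 SD shift and correlations of 0.3 to 0.5. At 100 per arm the bias falls to about 0.02 to 0.04 SD. Residual bias and an unplanned final model are the clearer harms; the inflation of type I error is small.

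A reader might infer a much larger effect by assuming stronger correlations or by quoting the largest imbalance that could escape a test. The document gives no correlation between any baseline variable and any outcome, so it does not support tying such figures to age, sector or education. The conclusion does not depend on which stated sample size is right. The change should be made, but the fault does not invalidate the pilot.

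**What to change.** Replace the adjustment sentence with one adjusted model per outcome, fixed before outcome data are examined and fitted whatever the baseline table shows. Include:
- arm;
- the baseline value of the outcome, where the preintervention survey collects it;
- age and sector of occupation (the matching factors);
- urban, periurban or rural stratum (the allocation factor);
- education, if the team judges in advance that it predicts the outcome.

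Remove the opening conditional and the restriction to variables showing baseline differences. Report the unadjusted comparison beside the adjusted one. If an unpublished analysis plan already fixes a covariate set, bring this sentence into line with it.

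**Cost.** Wording, and a few degrees of freedom. For example, sector in five groups (an assumption, borrowed from the business types listed for the Aim 1 interviews) takes 4, stratum 2, age 1 and baseline outcome 1. That is 8 in all, leaving 147 − 8 = 139 of the residual degrees of freedom at 150 women, or 117 − 8 = 109 at 120, before education. Area stratum is an LGA-level variable, so if the analysis also allows for clustering its cost falls on the number of LGAs, which the article does not state.

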### Ethical Considerations

The project will follow international research standards and be guided by the Principles for Global Health Research by the Canadian Coalition for Global Health Research. Ethics approval has been obtained from the Oyo State Ministry of Health Research Ethics Committee (reference number: NHREC/OYOSHRIEC/10/11/22), University of Ibadan and University College Hospital Ethics Committee (reference numbers: UI/EC/23/0256 and UI/EC/24/0809), and McGill University Ethics Committee (reference number: A11-B42-23A). Written informed consent or assent will be obtained from all participants before their enrollment into the study. Participants aged <18 years will be required to provide assent, while informed consent will be obtained from their parents. No names or any other forms of identification will be used in publications or reports resulting from the study without the permission of the participants. In keeping with recommendations for digital storytelling, participants will have the choice of identifying themselves and sharing their testimony. The consent and assent forms, interview guides, and questionnaires have been translated to Yoruba, the local language of the study location, using World Health Organization–recommended translation and back-translation procedures. This has been done to ensure that participants understand the study procedure fully and make an informed decision about whether to participate or not. Participants will be compensated monetarily for their time participating in this study as well as their transportation costs. This compensation will range from 2000 Nigerian naira to 10,000 Nigerian naira depending on the number of hours of participation. The conversion rate is 1 naira=US $0.00062).

### Data Management

All data will be digitally stored on the secure servers of the University of Ibadan and McGill University. Data will be stored in nonproprietary file formats wherever possible. All data will be anonymized and delinked from identifying information to ensure privacy and confidentiality. Knowledge translation materials will be openly available and uploaded to the International Development Research Centre repository. Scientific publications will be available open access.

### Integrated Knowledge Translation

Table 2 lists target groups for the research project and the knowledge mobilization strategies that will be used to engage them.

Knowledge mobilization strategies have been continuously further refined based on the input of other stakeholders. The principles of coproduction and equity have been guiding knowledge mobilization activities (eg, plain language summaries will be created for self-employed young women and tailored summaries for policy makers and associations). Our project steering committee has also been advising us on knowledge translation for scale and impact. In summary, our knowledge translation will guide Oyo State, Nigerian, and global efforts to enhance the resilience, health, and well-being of self-employed young women against significant disruptive life events.

**Table 2 table2:** Integrated knowledge mobilization strategies.

Knowledge users	Strategies
Self-employed young women	Involvement of self-employed young women in the development, implementation, and dissemination of the findings of the project Presentation of findings by “experts by experience” to associations and groups that the self-employed young women belong to Dissemination of videos created through digital storytelling
State, regional, and national policy and decision makers	Involvement of state and regional policy makers in the design and implementation of the project Targeted dissemination of policy briefs, intervention guidelines, digital storytelling videos, and peer-reviewed articles to policy makers Meetings and seminars with policy makers to inform them of the findings of the project and advocate for the scale-up of coproduced interventions
Scientific community and researchers	Peer-reviewed publications Conference presentations
General public	Dissemination of the findings of the project through press releases, social media platforms, and web content, as well as open-access publications

## Results

The recruitment of participants for the situational analysis phase of the project began in May 2023 and ended in January 2024. The recruitment of participants for the pilot study began in November 2024 and will be completed in January 2025. Data collection will be completed in November 2025. Table 3 gives details on the status of the various components of the study.

**Table 3 table3:** Status of various components of the Advancing Resiliency in Self-Employed Young Women in Nigeria (ARISE&WIN) study.

Activity	Status
Semistructured interviews with self-employed young women and men	Interviews have been conducted and are being analyzed.
Quantitative secondary data analysis	Analysis of secondary data is ongoing.
Scoping review	We are currently conducting full-text screening.
Digital storytelling	Digital stories have been created and disseminated. We are writing our analysis of these stories and their reception.
Systematic review	We are extracting data and conducting risk of bias assessments for selected studies.
Focus group discussions with self-employed young women and members of their support network and key informant interviews with policy makers	Interviews have been conducted and are being analyzed.
Policy analysis	Policies have been analyzed. We are writing the results.
Theory of Change and coproduction workshops	Theory of change and coproduction workshops have been conducted.
Pilot trial of the intervention packages	The intervention packages are currently being delivered. Data collection will be completed in November 2025.

## Discussion

This is a gender-transformative project that will provide a greater understanding of the impact of the COVID-19 pandemic and other significant disruptive life events on the working lives and well-being of self-employed young women in Nigeria and the norms, attitudes, and structures that perpetuate gender inequity. Through a collaboration between the researchers, self-employed young women, policy makers, and other relevant stakeholders, the project will result in suitable and contextually appropriate gender-transformative interventions to enable young women to better cope with events that disrupt their work and well-being and improve their income security; their mental, physical, and social health; and their social support system. The interventions that will be developed will consider the perspectives and needs of women who are particularly marginalized, including those with mental and physical disabilities and those with little or no formal education. These interventions will differ from previous interventions for self-employed young women in this context because they will be coproduced, and intentional attention will be paid to gender dynamics in their design. The results of the pilot study will be used to ascertain the feasibility, acceptability, cost, and potential effectiveness of the coproduced intervention packages. The results of the pilot study will be used to refine the intervention packages in preparation for a large-scale efficacy trial.

Research and policy-related findings will be disseminated through peer-reviewed articles, policy briefs, intervention guidelines and manuals, press releases, social media, and web content. Multistakeholder meetings involving self-employed young women, government officials, impact investors, researchers, and other relevant individuals will be organized to disseminate and discuss the findings from the various stages of research over the course of the project. The partnership with Oyo State Ministry of Women Affairs and Social Inclusion, SMEDAN, and the Centre for Support of Women in Unpaid and Informal Employment in Nigeria in the development and rollout of this project will enhance the uptake and scale-up of the intervention. Our partnership with the Development Agenda for Western Nigeria Commission, an organization responsible for facilitating policy design and implementation for the 6 states in the southwest of Nigeria, will enable the scale-up of the policy findings from this project to other Nigerian states.

This project will build capacity among self-employed young women to coproduce and contribute to research and policy development. The project will also develop their capacity by improving their knowledge and skills on how to run a business, improve their knowledge on how to take care of their health, and enable them to harness existing networks to better support their businesses through disruptive events. The project will enhance the capacity of the research team and policy makers in coproduction so that research and policy have greater relevance to the lived realities of young, self-employed Nigerian women.

Ultimately, this project will help advance Sustainable Development Goal (SDG) 3 “to ensure healthy lives and promote well-being for all at all ages”; SDG 5 to “achieve gender equality and empower all women and girls”; and SDG 8 “to promote sustained, inclusive, and sustainable economic growth, full and productive employment, and decent work for all.” It will also advance SDG 1 “nobody will live in extreme poverty,” SDG 2 “end hunger and achieve food security,” and SDG 16 “promote peaceful and inclusive societies for sustainable development.”

## Appendix

Multimedia Appendix 1 Interview guides for semistructured interviews and focus group discussions.

Multimedia Appendix 2 Scoping review sample search strategy.

Multimedia Appendix 3 PRISMA-ScR (Preferred Reporting Items for Systematic Reviews and Meta-Analyses Extension for Scoping Reviews) checklist.

Multimedia Appendix 4 Systematic review sample search strategy.

Multimedia Appendix 5 PRISMA-P (Preferred Reporting Items for Systematic Reviews and Meta-Analyses Protocols) checklist.

Multimedia Appendix 6 Peer review report by the International Development Research Center (Canada).

## Abbreviations

ARISE&WIN: Advancing Resiliency in Self-Employed Young Women in Nigeria
COVID-19 NLPS: COVID-19 National Longitudinal Phone Survey
FGD: focus group discussion
GHS: Nigerian General Household Survey
LGA: local government area
LMIC: low- and middle-income countries
PRISMA: Preferred Reporting Items for Systematic Reviews and Meta-Analyses
RCT: randomized controlled trial
SDG: Sustainable Development Goal
SMEDAN: Small and Medium Enterprises Development Agency of Nigeria
